## Abstract

**Background:**

There are currently no approved pharmacotherapies for managing methamphetamine dependence. *N*-acetylcysteine (NAC) has been found to reduce the craving for methamphetamine and other drugs, but its effect on methamphetamine use and other clinically related endpoints are uncertain. The N-ICE trial is evaluating the safety and efficacy of NAC as a take-home pharmacotherapy for methamphetamine dependence.

**Methods/design:**

This is a two-arm parallel double-blind placebo-controlled three-site randomised trial (ratio 1:1) using permuted block randomisation, with variable block sizes. It is stratified by site, sex and whether the methamphetamine is injected or not. Participants (*N* = 180; 60 per site) need to be dependent on methamphetamine, interested in reducing their methamphetamine use and not currently receiving treatment for substance use disorders. The trial is being conducted in outpatient settings in Melbourne, Geelong and Wollongong, Australia. Participants will receive either 2400 mg oral NAC or a matched placebo, delivered as a take-home medication for 12 weeks. Two 600 mg capsules are self-administered in the morning and two more in the evening. Adherence is being monitored using eCAP™ medication bottle lids, which record the date and time of each occasion the bottle is opened. The primary outcome is methamphetamine use during the 12-week trial medication period, measured as (a) days of use, assessed using the timeline followback, and (b) methamphetamine-positive saliva tests, taken weekly. Secondary measures include weekly assessment of methamphetamine craving, severity of methamphetamine dependence, methamphetamine withdrawal symptoms and psychiatric symptoms (depression, suicidality, psychotic symptoms and hostility). Adverse events are monitored at each weekly assessment. Tolerability is assessed using the Treatment Satisfaction Questionnaire for Medication.

**Discussion:**

The N-ICE trial is the first clinical trial to assess whether NAC can reduce methamphetamine use. This trial will improve our understanding of the potential utility of NAC in managing methamphetamine dependence and clinically related outcomes. If found to be effective, take-home NAC could be a potentially scalable and affordable pharmacotherapy option for treating methamphetamine dependence.

**Trial registration:**

Australian and New Zealand Clinical Trials Registry, ACTRN12618000366257. Registered on 29 May 2018.

**Electronic supplementary material:**

The online version of this article (10.1186/s13063-019-3450-0) contains supplementary material, which is available to authorized users.

## Introduction

Methamphetamine (“ice”) use has become a global health concern [1] and methamphetamine dependence is now a major contributor to the burden of disease [2]. Hence, there is an urgent need for scalable and cost-effective treatment options [3]. However, currently there are no approved pharmacotherapies for treating methamphetamine dependence or withdrawal [3, 4], or its psychiatric sequelae [5, 6], with existing treatment options entirely reliant on psychosocial interventions [3]. Although these can provide a modest benefit [7, 8], they can be resource intensive to deliver [9] and are typically accessed by only a minority of consumers, particularly in rural and resource-poor settings [10, 11]. Pharmacotherapy may be a potentially scalable and cost-effective treatment option that could dramatically increase treatment coverage.

*N*-acetylcysteine (NAC) is a novel non-agonist pharmacotherapy that targets changes in glutamate function in the nucleus accumbens, which are thought to underpin drug craving and drug seeking [12]. NAC has been shown to reduce cravings for various drugs, including cocaine, tobacco, cannabis and methamphetamine [13]. However, evidence of reduced substance use is mixed [14, 15] and derives mainly from preclinical research and open-label and small-scale trials [16–18]. One small-scale crossover trial has demonstrated significant reductions in the craving for methamphetamine [19], but no trials have explored whether such reductions in cravings translate into clinically meaningful reductions in methamphetamine use amongst people who are dependent on the drug.

NAC may also convey a therapeutic benefit in managing the psychiatric sequelae associated with methamphetamine dependence. In addition to its potential for reducing drug cravings, pre-exposure to NAC reduces methamphetamine-related neurotoxicity [20]. These neurotoxic changes manifest as reduced dopamine and serotonin transporter density in the frontal, striatal and limbic regions [21, 22], which correlate with psychiatric symptoms, including hostility, in chronic methamphetamine users [23, 24]. Previous clinical trials have suggested that NAC can reduce psychiatric symptoms in the context of bipolar disorder, schizophrenia and major depression [25]. However, the potential therapeutic mitigation of psychiatric symptoms amongst people who use methamphetamine [26, 27] has not been explored.

NAC’s well-established safety profile means that it can be delivered as a take-home medication [28], making it a potentially scalable and cost-effective treatment option. It is no longer under any patent restrictions, further enhancing its roll-out and take-up. Known adverse reactions include gastrointestinal upsets and rash [29], which have not been significantly elevated relative to the placebo in current NAC trials for substance use disorders [30]. The seemingly generic effect of NAC on drug craving suggests that it may also be helpful in managing polysubstance dependence.

### Aims and hypotheses

The aim of the current trial is to test the safety and efficacy of NAC as a pharmacotherapy for methamphetamine dependence using a double-blindplacebo-controlled randomised controlled trial. The trial will recruit 180 participants, who will receive either 12 weeks of oral NAC (2400 mg daily) or matched placebo. This is a phase IIb trial that is powered to confirm whether NAC has a clinically relevant benefit on methamphetamine use. The comparator condition is a matched placebo, with all participants provided with a minimal form of intervention (a self-help booklet), due to the lack of readily available standardised effective treatment options for methamphetamine use.

The primary hypothesis is that daily oral NAC delivered as a take-home medication will reduce methamphetamine use measured as (a) days of methamphetamine use and (b) methamphetamine-positive weekly saliva tests, during 12 weeks of active treatment relative to the placebo. The secondary hypotheses are that daily oral NAC delivered as a take-home medication will, relative to placebo:reduce the severity of methamphetamine dependence, the craving for methamphetamine, methamphetamine withdrawal symptoms and psychiatric symptoms (depressive symptoms, suicidality, psychotic symptoms and hostility)have an acceptable adverse event (AE) profilenot significantly increase the use of other substances (including alcohol, tobacco, cannabis, heroin and cocaine).

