### Other assessments

#### Polysubstance use

The polysubstance use measure is the percentage of days using drugs from other classes (tobacco, alcohol, cannabis, cocaine, ecstasy, hallucinogens, inhalants and heroin) for the 28 days prior to assessments 0, 4, 8 and 12, assessed weekly using the TLFB, and averaged across drug types.

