### Statistical considerations

#### Sample size estimation

The sample size of 90 participants per treatment arm is designed to detect a mean between-group difference of 3.5 days versus 6.0 days of methamphetamine use per month during the 12-week trial medication period with at least 80% power at *p* < 0.025 (0.05 / 2 to accommodate two primary outcome measures) and with 20% attrition (i.e., a final sample of at least 72 participants per treatment arm). The expected effect size is based on data from the Methamphetamine Treatment Evaluation Study (MATES) [42]. Participants who did not receive treatment in that cohort showed a reduction in methamphetamine use from a mean (standard deviation) of 12.8 (7.4) days per month at baseline to 6.0 (6.7) days per month at the 12-weekfollow-up. Our estimate of a minimal clinically meaningful reduction in use is based on outcomes for outpatient counselling derived from MATES: 11.2 (8.8) days per month to 3.5 (6.9) days per month at 12 weeks. Our estimate of 20% attrition is based on our previous research [42, 50, 51]. No interim analyses are planned. Statistical power was estimated using the SAMPSI command in Stata (Version 14.2, StataCorp LLC, College Station, Texas).

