#### Efficacy analysis

All tests will be two-sided with significance set at *p* < .025 for each of the two primary endpoints and *p* < .01 for each of the secondary endpoints. Significance for all other tests will be set at *p* < .05. The analyses will be conducted blind to condition.

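### A non-significant result on an eight-class average is weak evidence that NAC does not raise use of any one named drug, yet the secondary hypothesis is worded so that such a result meets it

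*Protocol article*

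**What the plan says.** Three places in the protocol article bear on this.

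- **Aims and hypotheses.** One secondary hypothesis is that NAC, relative to placebo, will not "significantly increase the use of other substances (including alcohol, tobacco, cannabis, heroin and cocaine"). Five drugs are named. No margin or confidence-interval criterion is attached.
- **Polysubstance use (under Other assessments).** The measure is the percentage of days of use in the 28 days before assessments 0, 4, 8 and 12. It covers eight classes, "tobacco, alcohol, cannabis, cocaine, ecstasy, hallucinogens, inhalants and heroin", and is "assessed weekly using the TLFB, and averaged across drug types". No weights are mentioned, so I read it as a simple mean.
- **Efficacy analysis.** The general rule begins "All tests will be two-sided with significance set at" the levels for the primary and secondary endpoints, and continues "Significance for all other tests will be set at *p* < .05". No test is written out for polysubstance use. Because the measure is listed outside the secondary endpoints, 0.05 appears to apply.

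The sample size section covers methamphetamine days only. Final analysis details are left to a statistical analysis plan that is not shown.

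**The concern.** Two features combine.

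First, the hypothesis is worded as the absence of a significant difference. Lack of precision then works in its favour: the noisier or more incomplete the data, the more easily it is met.

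Second, the hypothesis names individual drugs but the measure is a single average over eight classes, three of which (ecstasy, hallucinogens and inhalants) are not in the hypothesis. Opposite changes can offset each other. The article gives a reason to expect some falls, since its Introduction says NAC reduces craving for cocaine, tobacco and cannabis. A rise in alcohol or heroin days could be masked by a fall in tobacco or cannabis days.

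At stake is a report that NAC did not increase other substance use when the analysis says little about any single drug. For a take-home medication in people who often use several drugs, that could be read as more reassurance than the data give.

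**Working it through.** **Plan's own figure.** There is none for other substance use: no SD, power or margin is stated. The sample size section gives 90 per arm and 20% attrition, and 90 × 0.8 = 72 reproduces its analysable number.

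**Inputs.** From the article: 72 per arm, eight classes, a 28-day window, two-sided 0.05. Assumed: an SD of the average of 5, 8 or 10 percentage points. For orientation, the article's methamphetamine SDs (6.7 and 6.9 days per month, about 6.8) are 6.8/28 = 24.3 points. If all eight classes had that SD and were uncorrelated, the average would have SD 24.3/√8 = 8.6. Nothing in the article says they do.

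**Step 1: signal.** A rise of x points in one class, with the others unchanged, moves the average by x/8.
- 20 points (5.6 of 28 days): 20/8 = 2.5 points.
- 2.5 days, the difference the trial is sized to detect for methamphetamine: 2.5/28 = 8.9 points, and 8.9/8 = 1.1 points.

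**Step 2: power, single time point, unadjusted.** SE = SD × √(2/72) = SD/6. Power ≈ Φ(shift/SE − 1.96).

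| SD of average | SE | Power, 20-point rise | Power, 2.5-day rise |
|---|---|---|---|
| 5 | 0.83 | 85% | 27% |
| 8 | 1.33 | 47% | 13% |
| 10 | 1.67 | 32% | 10% |

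At 0.01, if the measure were treated as a secondary endpoint, power for the 20-point rise is 66%, 24% or 14%.

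**Step 3: what a null result leaves open.** The 95% half-width is 1.96 × SD/6 = 1.6, 2.6 or 3.3 points. Multiplied by 8, an estimate of exactly zero on the average is still compatible with a rise of about 13, 21 or 26 points in one class (3.7, 5.9 or 7.3 days per 28), if the other classes do not change.

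**Step 4: baseline and three repeats.** Suppose the analysis compares the mean of assessments 4, 8 and 12 with assessment 0, with a common correlation ρ. The variance is then multiplied by (1 + 2ρ)/3 + 1 − 2ρ = (4 − 4ρ)/3.
- ρ = 0.5, factor 0.67: power for the 20-point rise is 96%, 63% or 45%.
- ρ = 0.7, factor 0.40: 99.7%, 84% or 66%. The one-class half-widths become about 8, 13 or 17 points.
- For the 2.5-day rise, ρ = 0.7 gives 56%, 26% or 19%.

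**Step 5: where the power is lost.** Dividing by eight shrinks the signal and that class's own noise equally. The loss comes from the noise of the other classes. Take assumed, uncorrelated SDs of 35 (tobacco), 30 (alcohol), 40 (cannabis), 8 (cocaine), 5, 5, 5 (ecstasy, hallucinogens, inhalants) and 12 (heroin). The sum of squares is 4008 and the SD of the average is √4008/8 = 7.9. Tobacco, alcohol and cannabis supply 3725/4008 = 93% of the variance, so rarely used classes add almost none. Unadjusted power:
- 20-point rise in cannabis: 47% on the average, 85% on cannabis alone.
- 10-point rise in heroin: 16% on the average, over 99% on heroin alone.

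**The case against.** The strongest reply has four parts.

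1. **The confirmation rule is inferred.** No sentence says that p of 0.05 or more will be taken as proof of no increase, no test is set out for this measure, and the analysis plan may add intervals or per-drug results. This stands as a limit. But the wording of the hypothesis and the averaged measure are already fixed in the article, and an analysis that simply follows them inherits the weakness.

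2. **The average is not blind.** A reader might infer that it cannot detect a sizeable rise in one drug. The figures do not support that: a 20-point rise has about 85% power at SD 5 even unadjusted, and 84% at SD 8 with baseline adjustment and ρ = 0.7. A reader might also suppose that little-used classes dilute the test further. They do not; their place in the divisor is already in the one eighth, and they add almost no variance.

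3. **The SDs are assumptions.** This stands, and is why a range is shown. The structural points (one-eighth weight, offsetting, no margin) do not depend on them.

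4. **The consequence can be overstated.** A reader might call this a safety hypothesis, or speak of opioid use in general. The article lists it as a secondary hypothesis, records adverse events separately, and names heroin only. Days of other substance use are recorded at every assessment, so class-level reporting remains possible. A formal margin in a phase IIb trial sized for another outcome is optional.

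**Conclusion.** The point holds as one of interpretation and choice of measure. As worded, the hypothesis is met by any non-significant result, and its only defined measure mixes five named drugs with three others so that rises and falls can offset. A non-significant average is therefore weak evidence against a rise in any one drug.

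How weak depends on quantities the article does not give. For a 20-point rise in one class at two-sided 0.05 and 72 per arm, power runs from 32% to 85% unadjusted over SDs of 10 to 5 points, and from 66% to 99.7% under the favourable repeated-measures case tried (ρ = 0.7). For a rise of 2.5 days it runs from 10% to 27% unadjusted and from 19% to 56% at ρ = 0.7, so it stays below conventional power throughout. All of this assumes that the other classes do not change; a fall in another class would lower it.

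The change is worth making before unblinding, but neither the primary analysis nor the trial's conduct is affected.

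**What to change.** - Reword the hypothesis as estimating the effect of NAC on other substance use.
- From the timeline followback data already collected, report the between-arm difference with a 95% confidence interval for each of the five named drugs: alcohol, tobacco, cannabis, heroin and cocaine. Keep the eight-class average as a summary.
- Do not conclude that there was no increase from p of 0.05 or more. Interpret the upper confidence limit for each drug. If the investigators want a formal claim, compare it with a margin they fix before unblinding; otherwise call the result inconclusive.

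**Cost.** Some wording and a few more models, with no new data. Several class-level analyses bring some multiplicity, which should be acknowledged when they are read. Some drugs will probably have to be reported as inconclusive. For example, at an assumed single-class SD of 24.3 points and no true difference, excluding a 10-point rise with 80% power (one-sided 0.025, unadjusted) needs 93 per arm, more than the 72 expected.

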## Methods/design

### Design

This is a three-site phase IIb randomised double-blindplacebo-controlledparallel-group trial. Participants will be recruited across three sites (*N* = 180; 60 per site) and randomly assigned (1:1) to receive either oral NAC 2400 mg daily or the placebo, for 12 weeks. Weekly assessments throughout the 12-week medication phase will be used to assess outcomes. The trial flow diagram is presented in Fig. 1. The trial protocol was developed in accordance with the Standard Protocol Items: Recommendations for Intervention Trials (SPIRIT) Statement (see Additional file 1 for the SPIRIT checklist).

**Fig. 1 Fig1:**
[figure not shown]
Trial flow diagram. NAC *N*-acetylcysteine

### Randomisation and blinding

Participants are randomised to the treatment or placebo arms in a 1:1 ratio using a permuted block randomisation schedule with variable block sizes, stratified by site (Melbourne, Geelong or Wollongong), gender (male or female) and main route of methamphetamine administration in the month prior to recruitment (injecting or not injecting). The randomisation sequence was generated a priori using an in-house custom program written by WL. A random seed, assigned by the data and safety monitoring board (DSMB) statistician, was used to generate the final randomisation schedule using this program. Allocation to treatment condition (placebo vs. NAC) is based on the participant’s unique study identifier, this being assigned by trial staff sequentially within each stratum on randomisation.

All trial staff, the trial statistician (WL) and investigators are blind to treatment allocation. The randomisation schedule is held by the trial site pharmacy and the DSMB statistician. Allocation to trial arm is done by the trial pharmacist according to the randomisation schedule (provided by the DSMB statistician) using the unique study identifier provided by the trial staff. Packaging is identical to conceal treatment allocation. A removable adhesive label indicates whether the medication is placebo or NAC.

Unblinding is done at the discretion of the DSMB, the trial investigators or the treating medical physician in a medical emergency. Trial investigators can unblind individual participants via a password-protected online portal.

### Setting and study population

Participants are being recruited via outpatient settings in Melbourne (Turning Point and Eastern Health), Geelong (Barwon Health) and Wollongong (Illawarra Drug and Alcohol Service) in Australia. All participants are volunteers. They provide written informed consent prior to participation (see Additional file 2 for the participant information sheet and consent form). Inclusion criteria are that participants must be aged 18–60 years, meet DSM-IV criteria for methamphetamine dependence, be seeking to reduce their methamphetamine use but are not currently undergoing substance use treatment (including pharmacotherapy for substance use disorders), are not in need of acute care for psychiatric or other medical conditions, do not have a primary psychotic disorder, are able and willing to comply with the trial protocol, and have no contraindications for NAC. Contraindications for receiving the trial medication include: previous hypersensitivity to NAC; use of medications containing NAC or thought to be hazardous if taken with NAC (e.g. carbamazepine and nitroglycerin); a known or suspected active systemic medical disorder including cancer or other medical condition that may exacerbate the risk of AEs from NAC (recent gastrointestinal ulcers or renal stones, epilepsy or history of seizures, asthma or atopy); and, surgery within the past 28 days. Further, participants must not be pregnant (confirmed at the eligibility assessment), lactating or planning to fall pregnant during the trial.

### Intervention

Randomised participants will receive 2400 mg per day of oral NAC or a matching placebo (microcrystalline cellulose), taken as two 600 mg capsules every morning and evening for 12 weeks. The trial medication is supplied by Pharmaceutical Packaging Professionals (PPP) Pty Ltd. It is encapsulated in white capsules, size 00, and bottled in identical 200 cm^3^ white round plastic wide-mouth packer bottles (2.3 in. in diameter and 4.3 in. in height) fitted with eCAP™ lids (see Adherence). As a minimal intervention, all randomised participants are provided with a complementary self-help booklet, *On Ice* (National Drug and Alcohol Research Centre, University of New South Wales).

### Schedule of activities and study procedures

The trial flow diagram (Fig. 1) shows the schedule of activities.

#### Recruitment and screening

Participants are recruited through advertisements (e.g., Facebook, media activity, and flyers in needle and syringe programs) and word of mouth. They are screened by phone. Potentially eligible participants are consented by trial staff and then undergo a face-to-face eligibility assessment (1.5 to 2 h in total) to confirm their eligibility and to obtain information on demographics, drug use and psychiatric history. All participants undergo a medical assessment to confirm further their eligibility prior to randomisation. Randomisation must occur within 28 days of eligibility being confirmed. Eligible participants are provided with a list of local health service providers and are free to access drug treatment and other health services during the trial. Ineligible participants are offered referral to local alcohol and other drug services.

#### Assessments

The eligibility assessment and assessment 0 are conducted at the trial site clinic. Weekly assessments (assessments 1–12) are scheduled thereafter (with a leeway of −2 days to +4 days). These may be done at a public venue convenient to the participant (e.g., a café or shopping mall) to enhance retention. They take around 40 min each. Detailed contact information is collected on all participants and text message reminders are sent prior to appointments to enhance follow-up rates. Saliva samples are taken at each of the follow-up assessments using a Quantisal Oral Fluid Collection Device™. Participants undergo a final medical assessment within 30 days of completing the trial or on discontinuation of their medication. All participants are provided with referral information for alcohol and other drug treatment services at the close of the study.

